**Methods:**

Thirty-six participants aged 18–65 years will be recruited having mechanical chronic shoulder pain on unspecific origin and meeting the inclusion criteria. These will be randomized to one of two interventions, (i) DN, manual physiotherapy and therapeutic exercise or (ii) sham DN, manual physiotherapy and therapeutic exercise. The protocol will cover 6 weeks of treatment, with a 6-month follow-up. Our main outcome measure will be the Visual Analogue Scale for pain.

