## Background

Shoulder pain is a common musculoskeletal problem, with an annual prevalence of 20 to 50%, being the main cause of non-traumatic upper limb pain. It presents a high chronicity and recurrence [1] and the symptoms persist for 6 to 12 months in 40 to 50% of patients [2]. However, there is no standard for the clinical definition of shoulder pain [3].

Clinical trials tend to use the term nonspecific shoulder pain due to the lack of agreement on diagnostic criteria, lack of specificity of clinical evidence, coexistence of multiple shoulder pathologies and lack of any diagnostic test that is considered a “gold standard” [4]. The most common signs and symptoms are localized in the deltoid, forearm and shoulder region, presenting shoulder stiffness and limited range of motion [5] which restrict daily living activities [6].

Shoulder Impingement Syndrome is the most common diagnosis in primary care [7–9] and although it is believed to be the cause of shoulder pain, there is no solid evidence to support this. Furthermore, the presence of calcifications, acromial bone spurs, subacromial swelling, degenerative rupture of the rotator cuff, tendon inflammation and signs of degeneration are prevalent in both healthy subjects and in subjects with shoulder pain [10–12] so its diagnosis alone would not justify the presence of symptoms.

Moreover, it has been shown that the presence of myofascial trigger points (MTrPs) in the shoulder muscles is a common condition in patients with shoulder pain [3], and may cause pain during muscle stretching, contraction or compression. These MTrPs are hyperirritable points in taut bands of skeletal muscle and are painful to compression, producing motor dysfunction and referred pain [13].

As many as 17 muscles are known to reproduce similar symptoms to those of other painful shoulder syndromes, including pain at rest, upon movement and sleep disorders [1, 13, 14]. Therefore, the presence of MTrPs has been suggested as an alternative explanation for shoulder pain, regardless of the presence of subacromial disorders [1, 14].

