Treatment of shoulder pain usually begins with conservative therapies such as rest, physical therapy, anti-inflammatory drugs (NSAIDs) and corticosteroid injections [15, 16]. However, current studies have shown the benefits of a multimodal treatment for shoulder pain including techniques such as dry needling, stretching, manual therapy, mobilization techniques, applying cold, home exercise, ischemic compression of MTrPs and ergonomic recommendations [1, 17].

The choice of treatment is often subjective and depends on the therapist’s skill and training, while therapeutic exercise programmes in combination with manual therapy techniques often show good results [5, 18]. A recent meta-analysis by Kietrys et al. [5] recommends using dry needling, compared against placebo, to reduce pain, following treatment, and at 4 weeks follow-up in patients with Myofascial Pain Syndrome of the Upper Quadrant. However, new studies to support this recommendation are required.

It has been suggested that the inclusion of dry needling, in a single session, within a multimodal physiotherapy programme for patients with post-surgery shoulder pain, produces improvements in on and range of motion [19]. However, we have not found similar studies in patients with chronic shoulder pain of unspecific origin.

Therefore, the main aim of this study is to determine the effectiveness of including dry needling in a manual physiotherapy and therapeutic exercise programme, for the treatment of chronic shoulder pain of unspecific origin. Our hypothesis is that by including a single session of dry needling in a manual physiotherapy and therapeutic exercise programme, treatment outcomes improve, reducing symptoms and improving function in patients with shoulder pain.

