### Participants

From the town of Alcalá de Henares (Madrid), aged between 18 and 65 years with chronic mechanical shoulder pain of unspecific origin, lasting at least 3 months and provided they give their consent after being informed about participation in the study. The recruitment of participants will be conducted via email for University of Alcalá workers and students and by placing posters in a number of social and sports centres around the city of Alcala de Henares, where information about the study and contact information will be provided. Subsequently, a first telephone interview will be conducted to clarify any doubts of the participants, and the first screening for inclusion in the study will be carried out.

Participants’ personal data will be numerically coded and stored in a computer database, which may only be accessed to by the physiotherapist in charge of participant randomization and blinding.

Informed consent, as well as all study information will be emailed to the participants. Subsequently, prior to data collection and baseline measurement, participants should sign the informed consent, which could be revoked at any time during the intervention.

Inclusion criteria:Chronic mechanical shoulder pain of unspecific origin lasting at least 3 months.Aged between 18 and 65 years.Presence of active trigger points or areas of mechanical hypersensitivity in the muscles to be treated (upper trapezius, infraspinatus, subscapularis and middle deltoids) with pain reproduced in one or more muscles.

Participants will be examined for the presence of active trigger points in the muscles selected by a clinician with more than 10 years of experience in the treatment of MTrPs. Diagnosis of MTrPs will be determined by the presence of the following criteria: [1] hypersensitive point in a palpable taut band, [2] visible or palpable local spasm in response to MTrP palpation, and [3] reproduction of referred pain by palpation of the sensitive spot. These criteria have shown good interexaminer reliability (κ, kappa between 0.84 to 0.88) when applied by an experienced evaluator [20].

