### Evaluations

During the baseline measurement, the following descriptive characteristics will be collected: (i) gender, (II) age, (III) weight, (IV) height (V) dominant hand, (VI) current occupation, (VII) sport. In addition, the following information concerning the affected shoulder will be collected: (I) painful side, (II) duration of pain, (III) prior illness, (IV) taking medication. The chronology of the evaluation of the primary and secondary outcome measures is shown in Table 3.

**Table 3 Tab3:** Chronology of primary and secondary outcome measures

Results										
	Baseline Week 1	Week 2	Week 3	Week 4	Week 5	Week 6	1 week post	1 month post	3 months post	6 months post
Primary										
VAS	✔	✔	✔	✔	✔	✔	✔	✔	✔	✔
DASH	✔						✔	✔	✔	✔
Secondary										
Dynamometry	✔	✔					✔	✔	✔	✔
Goniometry	✔	✔					✔	✔	✔	✔
Algometry	✔	✔	✔				✔	✔	✔	✔

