### Statistical analysis

Data analysis will be carried out following the evaluation standards of the design of experimental studies with a control group. The experimental group (dry needling + manual physiotherapy and therapeutic exercise) will be compared with the control group (sham dry needling + manual physiotherapy and therapeutic exercise).

Data will be analysed using SPSS v.22 software for Windows. All statistical tests will be carried out considering a confidence interval of 95% (*p*-value <0.05) to determine the effectiveness of the 2 interventions by the method of intention to treat. Prior to statistical comparisons, all data will be analysed to determine the distribution of normality by the Shapiro-Wilk test. Subsequently, the homogeneity of the two intervention groups will be studied using Student’s t test for independent samples for data conforming to normal and the Mann-Whitney test for data that do not. The sex variable will be studied through Pearson χ2 or Fisher’s exact test, if the former cannot be used. Then a descriptive analysis of the data for the dependent variables will be performed. In these analyses, the mean and standard deviation (SD) for the dependent variables with normal distribution will be calculated. For variables that do not conform to normal, the data will be expressed with the median and first and third quartiles.

For the sex variable, frequencies are used. The existence of differences within each group will be determined, taking into account each group in isolation, between the different measurements (baseline and one week after dry needling; and post-treatment: at one week, at one month, at 3 months and at 6 months) in each of the study variables. In the VAS variable, measurements will also be taken in the treatment sessions; 2nd week, 3rd week, 4th week, 5th week, 6th week, using ANOVA for repeated measures, supplemented with simple and Helmert-type contrasts for variables that follow normal or Friedman’s ANOVA test, supplemented by Dunn’s multiple comparison test for those variables that will not conform to normal. ANCOVA will be performed to see the effect through different analyzes of the results and to intensify statistical power of the study. For this, the existence of a linear relationship and the homogeneity between the crude and basal scores of the dependent variables will be previously studied.

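### Before-after tests inside each arm are placed under the aim of showing effectiveness, which they cannot show without an untreated arm, and the plan does not say that the between-arm comparison alone governs the conclusion

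*Protocol article*

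**What the plan says.** The Background frames a question about added value: "the main aim of this study is to determine the effectiveness of including dry needling in a manual physiotherapy and therapeutic exercise programme". The abstract gives the two arms as "i) DN, manual physiotherapy and therapeutic exercise or (ii) sham DN, manual physiotherapy and therapeutic exercise", so they differ only in real versus sham needling.

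The Statistical analysis section opens by saying that the experimental group will be compared with the control group. It then gives one purpose for all statistical tests, judged at p < 0.05: "to determine the effectiveness of the 2 interventions by the method of intention to treat". After the baseline comparisons and a separate descriptive step, it plans the following for every study variable: "The existence of differences within each group will be determined, taking into account each group in isolation, between the different measurements". The method is given as "using ANOVA for repeated measures, supplemented with simple and Helmert-type contrasts for variables that follow normal or Friedman’s ANOVA test", the latter followed by Dunn's multiple comparisons. The visits run from baseline to 6 months after treatment. An ANCOVA is also announced.

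The last part of the section defines differences from baseline and compares them between the arms, with effect sizes. No sentence ranks this comparison above the within-arm tests or limits what the within-arm tests may be used for.

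**The concern.** The stated purpose refers to the effectiveness of each of two interventions. This design cannot measure that, because neither package is compared with no treatment. What randomisation does identify is the contrast between real and sham needling on top of the same programme. Testing each arm in isolation sets that control aside.

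Two misreadings become possible. A significant fall in pain in an arm could be reported as showing that the package is effective, when patients may have improved without it. And a significant result in the needling arm beside a non-significant one in the sham arm could be reported as a needling effect, when two identical arms of this size would often differ in that way by chance.

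**Working it through.** **What can be taken from the protocol**

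- Patients per arm: the Sample size section gives 28 before losses and 36 after, so 14 or 18 per arm.
- Significance level: 0.05.
- Natural course: the Background says "the symptoms persist for 6 to 12 months in 40 to 50% of patients". This concerns shoulder pain in general, and the care received is not stated.
- Population: "chronic mechanical shoulder pain of unspecific origin, lasting at least 3 months".
- Clinically relevant VAS difference: 13 to 14 mm (Primary outcome measures).

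The protocol gives no spontaneous recovery rate for these patients and no SD of VAS change. The size of the problem therefore has to be shown over a range of assumptions.

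**Step 1: how far the persistence figure carries.** The complement of 40 to 50% is 50 to 60%. Suppose that persistence is counted from onset, and that a share S of patients still has pain at 3 months (S is assumed). Later recovery among patients who could enter the trial is then 1 − (0.40 to 0.50)/S:

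| S | Recovery after month 3 |
|---|---|
| 0.6 | 17 to 33% |
| 0.8 | 38 to 50% |
| 1.0 | 50 to 60% |

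So 50 to 60% is an upper bound for the enrolled patients, and 20 to 40% is a more cautious working range.

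**Step 2: within-arm test with no treatment effect.** Assume that recovery lowers the VAS by 40 mm and that the SD of change is 25 mm. For recovery share r, the mean fall is 40r. The noncentrality of a paired t test is 40r/(25/√n). With n = 14 the standard error is 25/√14 = 6.68 mm. The probability of two-sided p < 0.05 comes from the noncentral t distribution with 13 degrees of freedom.

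| Recovery r | Mean fall | Noncentrality | P(significant), n = 14 | n = 18 |
|---|---|---|---|---|
| 20% | 8 mm | 1.20 | 0.20 | 0.25 |
| 30% | 12 mm | 1.80 | 0.38 | 0.48 |
| 40% | 16 mm | 2.39 | 0.60 | 0.73 |
| 50% (near the upper bound) | 20 mm | 2.99 | 0.79 | 0.89 |

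With n = 14, an SD of 20 mm gives 0.28, 0.55, 0.79 and 0.93, and an SD of 30 mm gives 0.15, 0.28, 0.46 and 0.64. At 40% recovery the mean fall already exceeds the 13 to 14 mm threshold.

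**Step 3: one arm significant, the other not.** For two identical arms, each significant with probability p, exactly one is significant with probability 2p(1 − p). With n = 14 and SD 25 mm this is 0.32 at p = 0.20, 0.47 at p = 0.38 and 0.48 at p = 0.60. None of that discordance carries information about needling.

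**Step 4: between-arm test.** A simulation used different assumptions: baseline mean 40 or 60 mm with SD 20 mm, recovered patients keeping 20% of their pain, and noise SD 15 mm. With no treatment effect and 17 to 33% recovery, within-arm tests were significant in 11 to 46% of trials with 14 per arm and in 16 to 60% with 18 per arm. An independent-samples test between arms stayed at about 5% at every recovery rate, because natural course acts on both arms alike.

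**The case against.** The strongest reply is that the plan does not rest its case for needling on within-arm change. The Background states an added-value aim, the Discussion asks about a greater effect, and the analysis section opens and closes with the comparison between arms. The sentence on effectiveness can be read as a general statement about significance level and intention to treat. Read literally, it would also turn the baseline homogeneity tests into tests of effectiveness. All this stands, and it limits the point. A reader might infer that the authors mean to take significance in one arm only as proof of a needling effect, but the protocol nowhere says so. What remains is that the within-arm analyses are planned as significance tests, separate from the descriptive step, under a stated purpose that they cannot serve, and with no order of precedence.

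A reader might also infer that, on the protocol's own figures, half or more of the patients would recover naturally. The Background does not support that. It does not say that the others recover, or that they do so untreated, and it does not describe patients with at least 3 months of pain. The Discussion stresses recurrence and persistence.

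It is fair, too, that the 40 mm and 25 mm are assumed, and that a paired t test stands in for the planned repeated-measures ANOVA or Friedman test. The probabilities show an order of magnitude and are not predictions. Nothing here relies on regression to the mean: the eligibility criteria set no minimum VAS score that would produce it by selection.

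Finally, a reader might think that chance imbalance in duration of pain biases the comparison between arms. It does not, since randomisation allows for such imbalance in the error rate. As an illustration, take a 20-point imbalance in short-duration patients, with recovery of 50% in short and 20% in long duration. The contrast shifts by 0.20 × 0.30 × 40 = 2.4 mm, against a standard error of 25 × √(2/14) = 9.4 mm.

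**Conclusion.** The point holds as one about stated purpose and interpretation. As written, the plan lets a before-after p-value inside one arm count towards effectiveness, although no arm is untreated and both share the same programme. Under the assumed 40 mm fall, 25 mm SD and 14 per arm, such a p-value falls below 0.05 with probability about 0.20 to 0.60 at 20 to 40% spontaneous recovery and no treatment effect. An independent between-arm test stays near 5%. The direction does not depend on the exact inputs: any average improvement unrelated to treatment pushes the within-arm rate above 5%.

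The randomised comparison is not invalidated, because it is already planned and does not depend on the within-arm tests. The 50 to 60% complement of the persistence figure should be used only as an upper bound.

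**What to change.** In the Statistical analysis section:

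1. Restate the purpose of the tests as estimating the effect of adding dry needling to manual physiotherapy and therapeutic exercise.
2. State that only the between-arm comparison supports conclusions on effectiveness.
3. Report within-arm changes as descriptive summaries with intervals and without p-values.

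Optionally, pre-specify duration of pain, which is already collected at baseline (Evaluations), as a covariate beside the baseline score in the planned ANCOVA. The reason would be precision, not correction of bias.

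The cost is small. The three changes are wording and need no new data, visits or patients; the sponsor gives up the within-arm p-values. The optional covariate costs one degree of freedom.

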### Sample size

The pain variable is chosen as the primary measurement of the study results. An effect size TE = 0.25 will be considered [21]. A correlation between repeated measures of 0.5 shall be assumed. Assuming the performance of 6 measurements -basal and a week after the dry needling, and post-treatment: at one week, at one month, at 3 months and at 6 months- in two treatment groups, sphericity correction will be determined at 0.5. With a statistical power of 0.95, with an alpha level of 0.05, a total sample size of 28 patients is estimated, and taking into account 25% for losses, a total of 36 patients needs to be reached, being 18 in both groups, using the Software Gpower 3.0.18 [22].

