### Primary outcome measures

The main result of this study will be the intensity of shoulder pain measured by ***Visual Analogue Scale (VAS) for pain***. Participants will mark the intensity of their pain on the VAS, consisting of a 100-mm long horizontal line, which is anchored by the classifications of “no pain” at the left end (score 0) and “worst pain imaginable” rightmost (score 10), asking to the participant for the most intense pain episode perceived meanwhile doing daily activity. The VAS has demonstrated the ability to detect changes in pain, establishing a minimal clinically significant difference at 13 mm [41, 42]. And in patients treated for rotator cuff disease a difference at 14 mm [43].

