For comparison between groups, a variable that we define as “difference” will be found; for each dependent variable, by subtracting the baseline measurement - at one week following needling, baseline - post 1 week, baseline - post 1 month, baseline - post 3 months and baseline - post 6 months (for the DASHe variable, the measurement will not be collected at one week after needling).

For the VAS variable, the “difference” variables will be found between baseline - week 2, week 3, week 4, week 5, week 6. To determine differences in dependent variables between the two intervention groups, the Student t test will be applied for related samples in variables whose data follow normal, in this case the effect size will be calculated according to the formula d = 2 t/√g. In the case of variables whose data do not follow normal, an analysis by the Mann-Whitney test will be performed and the effect size will be estimated according to Grissom procedures according to the formula.

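### The stated 0.95 power belongs to a two-group, six-occasion repeated-measures test, and the analysis section states no such between-arm test

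*Protocol article*

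**What the plan says.** **Protocol article, Sample size.** "The pain variable is chosen as the primary measurement of the study results". The calculation then sets the effect size ("An effect size TE = 0.25 will be considered", taken from a cited source) and the correlation ("A correlation between repeated measures of 0.5 shall be assumed"). It counts six occasions in two groups ("Assuming the performance of 6 measurements -basal and a week after the dry needling, and post-treatment", followed by four post-treatment visits), with a sphericity correction of 0.5, alpha 0.05 and power 0.95. The result is 28 patients, raised to 36 (18 per arm) for losses. The effect being tested is not named.

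**Protocol article, Statistical analysis.** Repeated-measures ANOVA, or Friedman for non-normal data, is assigned to changes over time inside one arm: "The existence of differences within each group will be determined, taking into account each group in isolation, between the different measurements". The between-arm comparison is a separate step. A change from baseline is formed for each visit and tested by a t test or Mann-Whitney: "To determine differences in dependent variables between the two intervention groups". For VAS the visits are weeks 2 to 6 and four post-treatment visits, nine in all. An ANCOVA is also announced, linked to baseline scores and meant to raise power, but its factor, its visit and its place in the conclusions are not given. No arm-by-visit term appears.

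**Protocol article, Primary outcome measures.** For the VAS the text cites prior work "establishing a minimal clinically significant difference at 13 mm", and 14 mm in rotator cuff disease. No VAS standard deviation is given.

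**The concern.** A power figure describes one test of one effect. Here the test that was sized and the tests that will compare the arms are different. A reader who sees 0.95 will attach it to the VAS comparison of real with sham needling, and the protocol gives no basis for that.

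The only repeated-measures analysis that is stated does not address the aim, which is the added value of dry needling. Both arms receive six weekly sessions of manual therapy and exercise, so both are expected to improve. A time effect inside one arm mixes the shared treatment, natural course and any needling effect. The section does not say that these within-arm results are descriptive only.

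At stake are the justification of the sample size and the identity of the primary comparison.

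**Working it through.** **Inputs.** From Sample size: effect 0.25 (read as Cohen's f, the usual G*Power input for this design), ρ = 0.5, m = 6, two groups, ε = 0.5, α = 0.05, N = 28 (14 per arm) before losses and 36 (18 per arm) recruited. From Primary outcome measures: 13 mm. Assumed, because the documents give none: VAS SD of 15, 20 or 25 mm.

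**1. Reproduce the stated figure.** For the within or within-between effect with two groups:

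- λ = f²·N·m·ε/(1−ρ), df1 = (m−1)ε, df2 = (N−2)(m−1)ε.
- ε = 1, N = 28: λ = 0.0625 × 28 × 6/0.5 = 21, df = 5 and 130, power 0.954. This reproduces 28.
- ε = 0.5, N = 28: λ = 10.5, df = 2.5 and 65, power 0.785.

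The 28 therefore comes from a two-group, six-occasion repeated-measures F test. The stated sphericity correction of 0.5 does not give 28; that is a separate error and this point does not rest on it.

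**2. Look for that test in the analysis.**

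| Stated analysis | Compares arms? | Uses all occasions jointly? |
|---|---|---|
| Repeated-measures ANOVA or Friedman, per arm | No | Yes |
| t test or Mann-Whitney on change scores | Yes | No, one visit at a time |
| ANCOVA | Not stated | Not stated |

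No row is the sized test.

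**3. What f = 0.25 means as a difference between arms.** With two equal arms, the interaction variance is one quarter of the variance over occasions of the between-arm difference. So f = 0.25 means that this difference has an SD over the six occasions of 2 × 0.25 = 0.5 (in units of the outcome SD). With no difference at baseline:

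- Constant difference Δ at the five later occasions: Δ·√(5/36) = 0.5, so Δ = 1.34 SD.
- Difference present at three of six occasions: Δ/2 = 0.5, so Δ = 1.0 SD.
- Linear rise from zero: 1.46 SD at the last occasion, 0.29 SD at the first after baseline.

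A constant 1.34 SD is 20, 27 or 34 mm at an SD of 15, 20 or 25 mm. It equals 13 mm only if the SD is 13/1.34 = 9.7 mm.

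**4. Power of the planned single-visit comparison.** The SD of change is SD·√(2(1−ρ)) = SD at ρ = 0.5. I used the exact noncentral t for two independent arms (the protocol labels the test as the paired form), with noncentrality d·√(n/2), 2n−2 degrees of freedom and two-sided 0.05. The F test in the last column takes the same difference as constant after baseline.

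| Difference | t test, 14 per arm | t test, 18 per arm | Sized F test, N = 28 (ε = 1 / 0.5) |
|---|---|---|---|
| 1.34 SD | 0.93 | 0.97 | 0.95 / 0.78 |
| 1.0 SD | 0.72 | 0.83 | 0.73 / 0.51 |
| 0.65 SD (13 mm at SD 20) | 0.38 | 0.47 | 0.34 / 0.24 |
| 0.5 SD | 0.25 | 0.31 | 0.21 / 0.15 |

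For 13 mm at an SD of 15, 20 or 25 mm, the single-visit test has power 0.60, 0.38 or 0.26 with 14 per arm, and 0.71, 0.47 or 0.33 with 18. Power of 0.95 needs 1.42 SD with 14 per arm or 1.24 SD with 18.

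Under the linear rise, power with 14 per arm runs from 0.12 at the first later occasion to 0.96 at the last. The choice of visit therefore decides the power, and none is named.

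**The case against.** The tempting stronger reading is that the planned tests have far lower power than the sized test. The figures do not support it. Compared at the same sustained difference, the single-visit t test has about the power of the F test at ε = 1, and more than the F test at the stated ε of 0.5. The low values (0.25 to 0.60) come from assuming a smaller effect, not from the choice of test. Power is clearly lower only at the weak visits of a varying profile. For the same reason, replacing the change-score tests with an omnibus arm-by-visit test would not recover power. A comparison of change scores between randomised arms is valid in itself. All of this stands.

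The ANCOVA may be intended as a baseline-adjusted comparison of the arms. If so it would help: about 0.98 with 14 per arm at 1.34 SD. But without a factor, visit or role it cannot be taken as the primary analysis, and it is not the sized test either.

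A reader might also infer that the plan will conclude from significance in one arm and not in the other. No sentence says so, and the section sets out a separate between-group procedure. What can be said is only that the within-arm tests are not labelled descriptive.

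Lastly, the protocol never claims to be sized for 13 mm, and the source of the 0.25 is not available here. The comparison in mm therefore shows what is left unstated; it does not prove a wrong target.

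**Conclusion.** The point holds as a mismatch. The 0.95 is the power of a two-group repeated-measures F test that the stated analysis does not contain, so it is wrong as a description of the between-arm comparison. The within-arm tests cannot fill the gap.

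The size of the discrepancy cannot be fixed from the document. At 14 per arm, single-visit power is about 0.93 if 0.25 means a sustained 1.34 SD difference, 0.72 at 1.0 SD and 0.25 at 0.5 SD. These figures assume ρ = 0.5, equal variances and correlations across visits, normal data, no baseline difference and no adjustment over the nine VAS comparisons. The figures in mm also rest on assumed SDs.

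**What to change.** 1. Name one primary between-arm analysis of VAS with its visit or contrast. Two suitable forms are a baseline-adjusted ANCOVA with arm as factor at a named visit, or a prespecified contrast from a joint model with arm, visit and arm-by-visit. If the joint model is chosen, say which contrast carries the conclusion; otherwise the reported test may again differ from the sized one.
2. State that the within-arm ANOVA and Friedman results are descriptive and are not used to judge the effect of dry needling.
3. Restate the power, or the detectable difference, of that analysis at the planned N. Give it in mm with its SD and correlation assumptions, beside the 13 to 14 mm threshold.

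The cost is rewording of two sections and one recalculation. It needs no extra patients or data, and SPSS fits either model. The downside is that the restated power may be less favourable than 0.95, and the team would then have to report it as it is.

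### No visit or single comparison is named for judging the VAS, while between-arm tests are prescribed at nine visits, each at p < 0.05 and with no hierarchy

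*Protocol article*

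**What the plan says.** The outcome is clear and its timing is not. The abstract states: "Our main outcome measure will be the Visual Analogue Scale for pain". The Primary outcome measures section repeats it: "The main result of this study will be the intensity of shoulder pain measured by" the VAS. Neither place names a visit. The hypothesis at the end of the Background says that "by including a single session of dry needling in a manual physiotherapy and therapeutic exercise programme, treatment outcomes improve", again without saying when.

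The Statistical analysis section compares the arms on differences from baseline. For all outcomes except DASHe these are one week after needling and then "baseline - post 1 week, baseline - post 1 month, baseline - post 3 months and baseline - post 6 months". For the VAS, in addition, difference "variables will be found between baseline - week 2, week 3, week 4, week 5, week 6". The test is a Student t test, or Mann-Whitney where the data are not normal. The threshold is general: "All statistical tests will be carried out considering a confidence interval of 95" per cent, given there as p < 0.05.

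The repeated-measures ANOVA with contrasts, and the Friedman test with Dunn's comparisons, are assigned to changes within each arm taken separately. ANCOVA is added without a visit or a rank. The Sample size section assumes six measurements in two groups "with an alpha level of 0.05".

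**The concern.** The nine visits answer different questions. Needling is given once, at the start of the first session. Week 2 therefore shows its early effect, one week after the last session shows what it adds to the six-week programme, and six months shows whether any gain lasts. Without a named comparison, an isolated week-3 difference and a sustained six-month difference could carry the same conclusion.

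The second issue is error control. Nine tests at 0.05 with no hierarchy give the main outcome nine chances of a significant result, and nothing in the text says which of them counts. The repeated-measures procedures do not act as a gatekeeper, because they are applied within each arm and not between arms.

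**Working it through.** **Inputs.** Statistical analysis section: nine VAS differences, p < 0.05 each. Sample size section: correlation between repeated measures 0.5; 28 evaluable patients (14 per arm); 36 recruited (18 per arm). Assumed: two-sided tests, since sidedness is not stated; and two-sample tests, since the arms contain different patients, although the text says "To determine differences in dependent variables between the two intervention groups, the Student t test will be applied for related samples".

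**Count of visits.** Needling is at session 1 and sessions are weekly, so one week after needling is the week-2 visit, in agreement with Table 3. Weeks 2 to 6 give 5 visits and the post-treatment assessments give 4, so 5 + 4 = 9.

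**The plan's own figure.** The protocol gives no familywise error to reproduce; its only computed figure is N = 28. For the within-between interaction of a repeated-measures ANOVA, reading the effect size of 0.25 as Cohen's f, λ = N f² m ε / (1 − ρ).
- With the stated ε = 0.5: λ = 28 × 0.0625 × 6 × 0.5 / 0.5 = 10.5 on 2.5 and 65 degrees of freedom. Power is 0.785, and 95% power needs N = 46.
- With ε = 1: λ = 21 on 5 and 130 degrees of freedom. Power is 0.954 at N = 28, so the printed figure matches only without the correction.

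This is a separate matter and does not alter the error rates below. It does show that the sample size belongs to a six-measurement analysis, which the Statistical analysis section does not use to compare the arms.

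**Correlation of the change scores.** With equal variances σ² and equal correlation ρ, Var(Yj − Y0) = 2σ²(1 − ρ) and Cov(Yj − Y0, Yk − Y0) = σ²(ρ − ρ − ρ + 1) = σ²(1 − ρ). The ratio is 0.5 whatever ρ is. The result below therefore does not depend on the protocol's 0.5 under this structure.

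**Reference if the tests were independent.** 1 − 0.95⁹ = 0.370.

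**Simulation under no effect.** Two arms, a baseline and nine follow-up scores, t tests on change from baseline:

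| Structure of the raw scores | Any visit p < 0.05 | Any visit p < 0.05 favouring needling |
|---|---|---|
| Equal correlation 0.5, 14 per arm | 0.27 to 0.28 | 0.14 |
| Equal correlation 0.5, 18 per arm | 0.27 | 0.14 |
| Autoregressive by visit, 0.5 to 0.7, 18 per arm | 0.23 to 0.25 | 0.11 to 0.12 |
| Autoregressive by visit, 0.8 to 0.9, 18 per arm | 0.21 to 0.22 | 0.10 to 0.11 |
| Only the five follow-up visits in the sample size, equal correlation 0.5, 18 per arm | 0.19 | 0.09 to 0.10 |
| One named visit | 0.05 | 0.025 |

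If the change scores themselves correlate 0.7 to 0.8, the two-sided figure for nine visits is about 0.17 to 0.20.

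**Power if a single visit is chosen.** Reading f = 0.25 as d = 0.5 for two groups at one visit (an assumption), a two-sided t test at 0.05 has power 0.25 with 14 per arm and 0.31 with 18. At d = 0.8 it has 0.53 and about 0.65. The stated power is 0.95.

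**The case against.** The strongest reply is that the protocol states no success rule. It does not say that one significant visit out of nine confirms the hypothesis, and multiplicity rules are often left to an analysis plan, which is not shown. This stands in part: the error rates are conditional on an any-visit reading. It does not dispose of the point. The comparison that decides the main outcome belongs in the protocol, and the text is not silent: it prescribes per-visit between-arm tests at 0.05 and ranks none of them.

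A reader might also infer that a useless session has a one-in-four chance of being declared beneficial. The documents do not support that. The hypothesis is directional, and about half of the 27% are visits at which sham looks better. The figure for a result favouring needling is about 14%, to be set against 2.5%. Nor do the documents support an upper figure near one in three: that would need change scores correlated about 0.3, which does not arise when raw scores have equal variance and equal correlation.

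Finally, it can be said that naming one visit is not free, because the sample size was not built for one visit, and that the choice of visit is a matter of judgement. Both statements are right and shape the recommendation.

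**Conclusion.** The point holds. No visit or single comparison is named for the main outcome, and nine between-arm VAS tests at p < 0.05 are prescribed without a hierarchy. If any one significant visit is read as support, the chance of at least one significant difference under no effect is about 27% in either direction. It is 23% to 27% under equal correlation or autoregressive correlation up to 0.7, and about 21% when autoregressive correlation is as high as 0.9. The chance of one favouring needling is about 14% under equal correlation. The corresponding values for one two-sided test are 5% and 2.5%.

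These figures rest on normal data, two-sided two-sample tests, complete follow-up of 14 or 18 per arm, and the any-visit reading, which the text leaves open but does not state. The lack of a named comparison does not depend on any of these assumptions.

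**What to change.** In the Primary outcome measures section and in the between-group part of the Statistical analysis section, name one primary between-arm VAS comparison, tested at 0.05. Two forms are reasonable:

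- **One visit.** For example one week post-treatment, the first assessment after the programme to which needling is added. The documents do not dictate this choice; another visit would serve if named in advance.
- **One longitudinal comparison.** A group-by-time comparison over the six measurements assumed in the Sample size section, which keeps the analysis in line with the design that was sized.

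State which test is used for that comparison. State also that the other VAS visits are secondary or descriptive and cannot support the hypothesis alone. This includes six months, unless it is placed in a declared hierarchy. Table 3 lists DASH under the primary heading while the text makes it secondary; that should be aligned in the same edit, or a second primary outcome remains.

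The cost is wording, with no added visit or measurement, and all nine estimates can still be reported with intervals. The downside is that a difference seen only at another visit can no longer be the main result. If a single visit is chosen, the 95% power must be restated for that test; at an assumed d = 0.5 it is only about 25% to 31% with the planned numbers. If the longitudinal form is chosen, N = 28 should be recalculated with the stated sphericity correction.
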